### Objectives/end points

The overall aim of the study is to determine the impact of the two diagnostic strategies on prevalence and transmissibility of infections. The hypothesis is that the parasite prevalence and density are reduced in arms 2 and 3 compared with the standard of care. More infections will be detected early and may therefore be abrogated before they develop into chronic asymptomatic infections with continuous gametocytaemia. As such the primary end point is parasite prevalence and density in each arm by molecular detection in the end of study cross-sectional survey. Secondary objectives and end points seek to evaluate the impact of the interventions after each season, and to define the contribution and infectivity of gametocytes in these infections, as detailed in box 3. Exploratory objectives aim to understand the detectability and transmissibility of infections, by exploring (1) Relationships between parasitaemia and transmission, and (2) Associations between infectivity and host characteristics, parasite characteristics or mosquito exposure (box 3).

Box 3Objectives and end pointsPrimary objective/end pointParasite prevalence and density between arms by molecular detection at the end of the study cross-sectional survey (time frame: month 18 (end of second transmission season; January–February 2020)).Secondary objectives/end pointsParasite prevalence and density by molecular detection at the end of year 1 cross-sectional survey (time frame: month 6 (end of first transmission season; January–February 2019)).Parasite prevalence and density by molecular detection at the end of the dry season cross-sectional survey (time frame: month 12 (prior to second transmission season; June 2019)).Gametocyte prevalence and/or density by molecular methods at the end of study cross-sectional survey (time frame: month 18 (end of second transmission season; January–February 2020)).Gametocyte prevalence and/or density by molecular methods at the end of year 1 cross-sectional survey (time frame: month 6 (end of first transmission season; January–February 2019)).Gametocyte prevalence and/or density by molecular methods at the end of the dry season cross-sectional survey (time frame: month 12 (prior to second transmission season; June 2019)).Gametocyte prevalence and/or density by molecular methods among *Plasmodium falciparum* infections during all visits in the study (time frame: throughout study, an average of 18 months).The number of incident infections/clinical incidence detected during community case management involving active weekly fever screening, monthly screening and treatment, and passive case detection (time frame: throughout study, an average of 18 months).Infectivity to mosquitoes of *P. falciparum* infections (time frame: throughout study, an average of 18 months).Exploratory objectives/end points:The detectability of infections by highly sensitive rapid diagnostic tests (time frame: throughout study, an average of 18 months).The relationship between the proportion of infected mosquitoes and gametocyte density (time frame: throughout study, an average of 18 months).The impact of infection characteristics on the transmissibility of infections to mosquitoes (time frame: throughout study, an average of 18 months).The impact of human host characteristics on the transmissibility of infections to mosquitoes (time frame: throughout study, an average of 18 months).Association between total parasite density and gametocyte density (time frame: throughout study, an average of 18 months).Malaria transmission potential based on measured gametocyte densities and the association between gametocyte density and mosquito infection rates (time frame: throughout study, an average of 18 months).Number of acquired clones based on genotyping (time frame: throughout study, an average of 18 months).The duration of infections in the dry season (time frame: months 6–12, between end of season survey January/February 2019 and end of dry season survey June 2019).To quantify mosquito exposure in relation to incident infections and transmission opportunities (time frame: throughout study, an average of 18 months).

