### Procedures

#### Study visits

At the start and end of each season, a cross-sectional survey will be performed concurrently in all enrolled compounds (online supplementary figure S1). These surveys will also include adults that are present in enrolled compounds but not participating in the interventions; additional informed consent will be obtained for this. In these surveys all individuals will have their axillary temperature measured and a finger prick blood sample taken for molecular assessment of gametocyte and parasite carriage (as detailed in table 1). In case of measured fever, the same finger prick blood sample will be used for malaria diagnosis by conventional RDT (first response malaria RDT, specific for *P. falciparum* and/or *P. vivax, P. ovalae* and *P. malariae*) and treatment will be offered as per national guidelines. Routine surveys will be conducted throughout the wet and dry seasons to assess parasite carriage, gametocyte carriage and infectivity to mosquitoes. These surveys will be performed on a subset of compounds each week on a rolling basis, so that each compound will be visited every 10 weeks. Finger prick blood samples will be taken and processed as detailed in table 1; one whole blood aliquot will be processed immediately for molecular detection of *P. falciparum* parasitaemia by quantitative PCR (qPCR) targeting varATS.^23^ qPCR-positive individuals (ie, those with parasites, not necessarily gametocytes) will be invited to donate blood for mosquito-feeding assays. The maximum number of feeding assays per day will be dependent on logistical feasibility. Asymptomatic infections that are detected by PCR will not be treated if unaccompanied by malaria symptoms, in line with national treatment guidelines. Routine surveys will continue throughout the dry season to allow a detailed assessment of the number of newly acquired infections when minimal exposure to infected mosquito bites is assumed.

10.1136/bmjopen-2019-030598.supp1Supplementary data

**Table 1 T1:** Sampling schedule; the table indicates the samples collected at each participant survey/visit

Sample type/procedure	Cross-sectional survey	Routine survey	Passive case detection	CCM	MSAT	DMFA
Axillary temperature and clinical assessment	X	X	X	X	X	
Dried blood spot (DBS)	X	X	X	X*	X	
Whole blood in RNA protect	X	X	X	X*	X	X
Whole blood for DNA	X	X	X	X*	X	X
Rapid diagnostic test (RDT)	X*		X	X*	X	
Highly sensitive RDT (HS-RDT)						X
Plasma						X
Blood smear			X†	X†	X†	X

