*Sampling only takes place if the subject has fever or history of fever in the last 24 hours.

†Sampling only takes place if the subject has a history of antimalaria treatment in the previous 3 weeks for microscopic confirmation of malarial infection.

CCM, enhanced community case management; DMFA, direct membrane feeding assay; MSAT, monthly screening and treatment.

In all three arms, clinical malaria episodes will be passively monitored at the local health facilities. Participants will be identified using study identity cards; for suspected malaria cases, temperature and clinical history will be recorded. Finger prick blood samples will be taken as detailed in table 1. Malaria diagnosis will be performed by RDT and infected subjects will be treated with artemether-lumefantrine (AL). For infections detected by community health workers during enhanced CCM (arms 2 and 3) or MSAT (arm 3) visits, the same procedure is used and samples are collected as detailed in table 1. For RDT or microscopy-positive infections detected at local health facilities or during the CCM or MSAT visits, when logistically feasible, the individuals will be invited to donate a blood sample for mosquito-feeding assays prior to treatment. For all mosquito-feeding assays blood samples will be collected and transported in a portable incubator or thermos flask to the insectary for direct membrane feeding assays (DMFAs).

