#### Laboratory assessments

DMFAs will be performed to determine infectivity to locally reared female *Anopleles coluzzii* mosquitoes, as described previously.^14^ Whole blood collected in lithium heparin tubes will be offered in duplicate to 50–60 starved mosquitoes via an artificial membrane feeder (400–500 µl per feeder). Fully fed mosquitoes will be kept at 27°C–29°C and maintained on a sucrose diet for approximately 1 week (6–8 days). Mosquito infection will be determined by dissection and assessment for the presence and density of oocysts by two independent microscopists. Infected midguts will be stored for molecular confirmation of infection and genotyping for a subset of guts.^14^

Parasite DNA and RNA will be extracted from whole blood samples collected in EDTA tubes. Parasitaemia will be assessed using a qPCR assay targeting the var gene acidic terminal sequence (varATS qPCR)^23^ and gametocyte density and sex ratio will be assessed using established PCR protocols.^32^ Whole blood samples will be evaluated by highly sensitive (HS)-RDTs and presence and quantification of HRP2 will also be determined using the bead-based Luminex (Austin, Texas, USA) platform.^33^ Multiplicity of infection will be determined in a selection of samples using merozoite surface protein (MSP)-genotyping^34^ or equivalent techniques.

Red blood cell polymorphisms that are associated with the likelihood of developing blood-stage (clinical) malaria infection, the severity of malaria infection or gametocyte production (haemoglobin C, haemoglobin S, α-thalassaemia and glucose-6-dehydrogenase deficiency)^35^ will be measured in baseline samples by multiplex luminex assay.^36^ In secondary analyses, antibody responses to parasite and gametocyte antigens will be determined by protein microarray^37^ and multiplex bead-based serological assays^38^ and associated with parasite carriage, clinical symptoms and infectivity. For a selection of samples functional transmission reducing immunity will be assessed by standard membrane feeding assay using plasma samples collected at the time of field-based DMFA.^39^

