
### Data analysis

For primary and secondary end points, parasite and gametocyte prevalences will be compared between arms using multivariate mixed-effects logistic regression models; parasite and gametocyte density will be assessed using multivariate mixed-effects linear regression models on log-transformed values. The number of incident infections will be assessed by Poisson regression and compared between arms. The proportion of infectious participants and proportion of infected mosquitoes will be assessed by logistic regression models. Analyses will take account of correlation of outcomes at the compound level and the matched randomisation scheme. There may be issues with convergence in mixed-effects models given the small number of subjects per compound. In this case, analysis based on compound level summaries will be performed. For exploratory end points, detected infections will be analysed in relation to the time and duration of infection, parasite and gametocyte prevalence and density, symptoms, complexity of infection, host characteristics, mosquito exposure and infectiousness to mosquitoes. Parasite density will be related to detectability by HS-RDTs. The association between gametocyte density and mosquito infection prevalence and intensity will be determined using an established Bayesian hierarchical model that incorporates the density of male gametocytes and gametocyte sex ratio.^40^ In exploratory end points, model fitting will be performed for different strata of infection characteristics (eg, complexity of infection, concurrent asexual parasite density and season) and host characteristics (eg, antigametocyte immune responses, age). Mosquito exposure by indoor and outdoor trapping methods will be associated with the likelihoods of incident infections and opportunities to transmit infections using comprehensive malaria transmission models.^41^

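### HS-RDT detectability is measured only in feeding-assay donors, some of whom enter because another malaria test was already positive; pooling the entry routes can overstate detectability at a given parasite density

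*Protocol article*

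**What the plan says.** **End point.** Box 3 (Objectives/end points) gives as its first exploratory item "The detectability of infections by highly sensitive rapid diagnostic tests", measured throughout the study.

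**Who is tested.** Table 1 (Study visits) marks the HS-RDT in the DMFA column and in no other. The Laboratory assessments section says "Whole blood samples will be evaluated by highly sensitive (HS)-RDTs" but names no further visit, so Table 1 defines the tested set.

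**How people become DMFA donors.** The Study visits section describes two routes:
- Routine surveys: "qPCR-positive individuals (ie, those with parasites, not necessarily gametocytes) will be invited to donate blood for mosquito-feeding assays".
- Facility, CCM and MSAT visits: "For RDT or microscopy-positive infections detected at local health facilities or during the CCM or MSAT visits, when logistically feasible", people are invited to donate before treatment. The Table 1 footnote on blood smears at these visits reads "Sampling only takes place if the subject has a history of antimalaria treatment in the previous 3 weeks for microscopic confirmation of malarial infection". This second route is therefore mainly conventional RDT positivity.

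**Analysis.** The Data analysis section states "Parasite density will be related to detectability by HS-RDTs". It does not restrict the analysis to one route or separate the two. The example strata given for exploratory model fitting (complexity of infection, asexual density, season, immune responses, age) do not include entry route.

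**The concern.** The first route selects on parasite DNA. The second selects largely on a positive result from another rapid test. A conventional-RDT-positive sample is very likely to be HS-RDT-positive too, so for those donors the question is partly answered by the way they were chosen.

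Relating the result to parasite density does not by itself remove this. At any given density the second route admits only infections that the conventional test found. If both tests respond to something besides current parasite density, those infections are also the ones an HS-RDT finds more easily. Antigen level is the obvious candidate: the Laboratory assessments section plans HRP2 quantification alongside the HS-RDT.

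At stake is one exploratory curve of HS-RDT detectability against parasite density. It could make the test look better than it would be among infections not already found by another test.

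**Working it through.** The protocol gives no sample size, precision or expected sensitivity for this end point, so there is no figure to reproduce. The check has two parts: whether selection survives conditioning on density, and how large the effect could be.

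**Inputs**
- From the document: conventional RDT limit 40 asexual parasites/µL (a simulation input, in the list of simulated interventions).
- Assumed: HS-RDT limit 10/µL; log10 antigen = log10 density + N(0, SD), with SD 0, 0.5 or 1.0; independent assay noise of 0.2 log10 for each test.
- Assumed: infections exposed to the test-selected route relative to the qPCR route at each density, k = 1 or 3. The document gives no split and says only that assays depend on logistical feasibility.

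**Formulas at density d**, with S = √(SD² + 0.2²):
- True detectability s = 1 − Φ((log10 10 − log10 d)/S)
- P(RDT+) = 1 − Φ((log10 40 − log10 d)/S)
- Share of donors from the test-selected route: w = k·P(RDT+) / (1 + k·P(RDT+))
- Pooled detectability = w·P(HS+ | RDT+) + (1 − w)·s, where P(HS+ | RDT+) is from the bivariate normal with correlation SD²/S²

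**Worked case, d = 10, SD 0.5, k = 1.** S = √0.29 = 0.539. P(RDT+) = 1 − Φ(0.602/0.539) = 0.132. w = 0.132/1.132 = 0.116. P(HS+ | RDT+) = 0.992. Pooled = 0.116 × 0.992 + 0.884 × 0.50 = 0.557.

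| SD | d (/µL) | P(RDT+) | True s | P(HS+ given RDT+) | w, k = 1 | Pooled, k = 1 |
|---|---|---|---|---|---|---|
| 0.5 | 2 | 0.8% | 9.7% | 97% | 0.8% | 10.4% |
| 0.5 | 10 | 13.2% | 50% | 99% | 11.6% | 55.7% |
| 0.5 | 40 | 50% | 86.8% | 99.8% | 33.3% | 91.1% |
| 1.0 | 2 | 10.1% | 24.7% | 99.6% | 9.2% | 31.5% |
| 1.0 | 10 | 27.7% | 50% | 99.8% | 21.7% | 60.8% |
| 1.0 | 40 | 50% | 72.2% | 99.9% | 33.3% | 81.5% |

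With k = 3 at 10/µL, w is 28.3% (SD 0.5) or 45.4% (SD 1.0), and the pooled figure is 64% or 73%.

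With SD = 0 the tests share nothing beyond density, so P(HS+ | RDT+) equals s and the bias is nil.

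**Routine-survey donors in arms 2 and 3.** Box 1 treats RDT-positive infections found by weekly fever screening in both arms, and by monthly testing regardless of symptoms in arm 3. Routine-survey donors there can be short of RDT-positive infections. In the limiting case where none is RDT-positive, detectability reads [s − P(RDT+)·P(HS+ | RDT+)] / [1 − P(RDT+)]. At 10/µL:
- SD 0.5: (0.500 − 0.132 × 0.992)/0.868 = 43%
- SD 1.0: (0.500 − 0.277 × 0.998)/0.723 = 31%

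The true value is 50% in both, so this bias runs downward.

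**The case against.** **The plan never says the routes will be pooled, and an unseen SAP may separate them.** This is fair, and it is why the point is that pooling *can* overstate detectability. But the article fixes the sampling scheme and states an analysis by density alone, and anyone following that text would combine the routes.

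**Infections found at facilities or by CCM and MSAT are infections too.** True, and they should be reported. They still cannot show how often an HS-RDT detects infections in general, because most were admitted on a related test.

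**The mechanism is assumed.** The article does not name the conventional RDT's target antigen, and the bias disappears if the tests share no variation beyond density. This stands as a condition of the point. Shared variation is plausible but not documented.

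**Stronger readings that the document does not support.** A reader might infer that many donors enter by the test-selected route; no count or split is given. A reader might also fix that share at 25%, 50% or 75%, take HS-RDT positivity as 100%, and use w + (1 − w)s to turn a true 50% into 62.5%, 75% or 87.5%. That arithmetic is correct, but it does not carry over to each density: few low-density infections are RDT-positive, so w falls with density. For the same reason, the idea that bias is worst at the lowest densities is not established; at SD 0.5 and 2/µL with equal pools it is under one percentage point.

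**Restricting to routine-survey donors is not neutral either.** This stands for arms 2 and 3, as the limiting case shows, and the remedy has to allow for it.

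**Conclusion.** The point holds as a minor one. The HS-RDT is run only on feeding-assay donors, part of that group is selected on a positive conventional RDT or microscopy, and the stated analysis by density takes no account of it. If the two tests share variation beyond parasite density, pooling raises estimated detectability at a given density.

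The direction rests on that shared variation. The size is not known. The illustration gives 6 to 11 percentage points at 10/µL with equal pools and 14 to 23 with a 3:1 pool, on assumed detection limits, antigen spread and pool ratios. At the very lowest densities it may be negligible.

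The end point is exploratory. No sample size rests on it, and no primary or secondary comparison is affected.

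**What to change.** State in the analysis plan that:
1. The main estimate of HS-RDT detectability, overall and by parasite density, uses only donors selected by qPCR at routine surveys.
2. That estimate is shown by arm, with arm 1 as the reference, because screening and treatment in arms 2 and 3 remove RDT-positive infections and can bias those arms downward. Arm 1 is the least depleted arm rather than a wholly untouched one, since passive detection and treatment operate in all three.
3. Donors selected by conventional RDT or microscopy are reported separately, by visit type, and not pooled into the main estimate.
4. The number of HS-RDT-tested donors by entry route and arm is reported.

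No new samples, visits or tests are needed; entry route only has to be carried into the analysis data set. The cost is fewer samples and wider intervals for one exploratory estimate, most of all when it is read in arm 1 alone.

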
### Data analysis

For primary and secondary end points, parasite and gametocyte prevalences will be compared between arms using multivariate mixed-effects logistic regression models; parasite and gametocyte density will be assessed using multivariate mixed-effects linear regression models on log-transformed values. The number of incident infections will be assessed by Poisson regression and compared between arms. The proportion of infectious participants and proportion of infected mosquitoes will be assessed by logistic regression models. Analyses will take account of correlation of outcomes at the compound level and the matched randomisation scheme. There may be issues with convergence in mixed-effects models given the small number of subjects per compound. In this case, analysis based on compound level summaries will be performed. For exploratory end points, detected infections will be analysed in relation to the time and duration of infection, parasite and gametocyte prevalence and density, symptoms, complexity of infection, host characteristics, mosquito exposure and infectiousness to mosquitoes. Parasite density will be related to detectability by HS-RDTs. The association between gametocyte density and mosquito infection prevalence and intensity will be determined using an established Bayesian hierarchical model that incorporates the density of male gametocytes and gametocyte sex ratio.^40^ In exploratory end points, model fitting will be performed for different strata of infection characteristics (eg, complexity of infection, concurrent asexual parasite density and season) and host characteristics (eg, antigametocyte immune responses, age). Mosquito exposure by indoor and outdoor trapping methods will be associated with the likelihoods of incident infections and opportunities to transmit infections using comprehensive malaria transmission models.^41^

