## Methods and analysis

### Study design

This study is a cluster-randomised trial to determine the impact of two interventions on parasite carriage, gametocyte carriage and infectiousness to mosquitoes. A total of 180 compounds (consisting of three to six enrolled participants) will be randomised to one of three study arms (60 compounds per arm): arm 1 - current standard of care with passively monitored malaria infections; arm 2 - standard of care plus enhanced CCM; or arm 3 - standard of care and enhanced CCM, plus monthly screening and treatment (MSAT), as detailed in box 1.

Box 1Study armsArm 1 (control): Standard of careStandard of care with passively monitored malaria incidence at local health facilities. Health facilities will be equipped with research staff and adequate supplies to ensure malaria diagnosis and treatment with the first-line antimalarial artemether-lumefantrine (AL) according to national guidelines.Seasonal malaria chemoprevention (SMC) in children <5 years of age implemented by the National Malaria Control Programme (monthly treatment with sulfadoxine-pyrimethamine + amodiaquine from July to October).Arm 2 (intervention): community case management (CCM)Standard of care (as in arm 1).SMC (as in arm 1).Enhanced CCM for malaria involving weekly active screening for fever using a research-grade thermometer by a trained health worker. A measured temperature ≥37.5°C or reported fever in the last 24 hours will prompt screening with a conventional rapid diagnostic test (RDT). RDT-positive individuals will be treated with AL according to national guidelines.Arm 3 (intervention): CCM + monthly screening and treatment (MSAT)Standard of care (as in arms 1 and 2).SMC (as in arms 1 and 2).Enhanced CCM (as in arm 2).MSAT regardless of symptoms with a conventional RDT. Screening will be performed by research staff with 25–35 days between screening rounds; RDT-positive individuals will be treated with AL according to national guidelines.

The study will take place over approximately 18 months covering two high-transmission seasons and the low-transmission season (dry season) in between. Throughout the study, entomological monitoring will take place to evaluate the local mosquito population and potential exposure to infected mosquitoes.

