**Figure 5 F5:**
[figure not shown]
Simulations predict the impact of interventions in arms 2 and 3 across age groups. Simulation of the impact of enhanced CCM (arm 2, green) and enhanced CCM+MSAT (arm 3, orange) relative to no intervention (arm 1, purple) on parasite carriage in young children, school-age children and adults. Lines indicate mean and shaded area the 95% observed interval of prevalence by PCR with sensitivity 4 parasites/µL across 500 stochastic realisations.

*SMC:* Administration of a curative drug with prophylactic protection for 30 days to children<5 years. Four rounds of SMC carried out each year starting June 30 with 30 days between rounds. Coverage was set at 80% per round and independent between rounds.
*ITNs*: *Estimated age dependent distribution*; 0–5 years=67%, 5–10 years=74%, 10–15 years=68%, 15–20 years=65%, and >20 years=71%.
*Passive case detection and health-seeking behaviour:* AL administered to uncomplicated and severe malaria cases with age-dependent distance-based health-seeking. Distances to the two study health facilities in Sapone and Pissy were calculated from the centre of each grid cell with exponential half-distance in coverage of 10 km. Maximum coverage was 50% for children under 5 years, 30% for individuals over 5 years and 80% for severe cases. Patients received treatment within 3 days of onset of clinical symptoms.
*Enhanced*
*CCM*
*in arms 2 and 3:* Modelled as continuous weekly active screening where fevers of 37.5°C or higher receive AL, beginning 30 June 2018 with 100% coverage.
*MSAT with RDT in arm 3:* Modelled as continuous monthly RDT testing (diagnostic sensitivity 40 asexual parasites/μL), with RDT-positive individuals receiving AL, beginning 30 June 2018 with 100% coverage.

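### The incident-infection end point counts what arm-specific case finding detects, so its between-arm rate ratio mixes detection effort with any true effect and is pushed upwards

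*Protocol article*

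**What the plan says.** Box 3 (Objectives/end points) lists as a secondary end point: "The number of incident infections/clinical incidence detected during community case management involving active weekly fever screening, monthly screening and treatment, and passive case detection". It is the only primary or secondary end point that counts incident infections. The Data analysis section says of it: "The number of incident infections will be assessed by Poisson regression and compared between arms". That section allows for compound-level correlation and for the matched randomisation. It names no detection route common to the arms.

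Box 1 (Study design) allocates the routes:

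- **Arm 1:** passive detection at the health facilities. This route is shared: "In all three arms, clinical malaria episodes will be passively monitored at the local health facilities".
- **Arm 2:** adds "Enhanced CCM for malaria involving weekly active screening for fever using a research-grade thermometer by a trained health worker", with a rapid diagnostic test (RDT) if fever is measured or was reported in the last 24 hours.
- **Arm 3:** adds a further route, every 25 to 35 days: "MSAT regardless of symptoms with a conventional RDT".

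The Study visits section also describes routine qPCR surveys on a rolling schedule, "so that each compound will be visited every 10 weeks", and cross-sectional surveys in all enrolled compounds. Neither is described as differing by arm, and neither is named in the incidence end point.

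**The concern.** A rate ratio between randomised arms estimates an effect on incidence only if an infection has the same chance of being counted in each arm. Here the interventions are themselves ways of finding infections, and the end point counts what they find. The routes are nested: arm 2 has everything arm 1 has and more, and arm 3 has more again. The bias from detection therefore runs upwards in arms 2 and 3. An infection that never causes fever has essentially no route into the arm 1 count but can be counted monthly in arm 3.

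Infections are also not cleared at entry (Ethical considerations), so early MSAT rounds can find infections that were already present. Adjusting for compound and matched group removes none of this.

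At stake is a named secondary result. Interventions that leave clinical incidence unchanged could be reported as raising it, and a real reduction could be hidden.

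**Working it through.** The article gives no rate, rate ratio or power for this end point, so there is no stated figure to reproduce. The check asks what ratio to expect when true incidence is the same in every arm.

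**Inputs from the article** (simulated interventions, listed under Figure 5)

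- Passive detection: "Maximum coverage was 50% for children under 5 years, 30% for individuals over 5 years and 80% for severe cases". I use *c* = 0.50 and *c* = 0.30.
- CCM: "Modelled as continuous weekly active screening where fevers of 37.5°C or higher receive AL, beginning 30 June 2018 with 100% coverage". This says that everyone is screened weekly. It does not say that every fever is caught.

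**Assumptions**

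- Fever lasts *d* = 1 to 5 days, and its onset is unrelated to the visit day.
- Passive and active capture are independent.
- Every febrile infection that is tested is RDT-positive.
- *c* = 0.80 is a variant for well-supported study clinics.

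**Step 1: chance of being counted, febrile infections**

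- Arm 1: *c*.
- Weekly visit: *q* = (*d* + 1)/7, where the extra day is the 24-hour recall. *q* = 1 is the upper bound.
- Arm 2: *p* = 1 − (1 − *c*)(1 − *q*).
- Expected ratio, arm 2 to arm 1, at equal true incidence: *p*/*c*.

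| Fever days | *q* | *c* = 0.50 (under 5) | *c* = 0.30 (over 5) | *c* = 0.80 (assumed) |
|---|---|---|---|---|
| 1 | 0.286 | 0.643/0.50 = 1.29 | 0.500/0.30 = 1.67 | 0.857/0.80 = 1.07 |
| 2 | 0.429 | 0.714/0.50 = 1.43 | 0.600/0.30 = 2.00 | 0.886/0.80 = 1.11 |
| 3 | 0.571 | 0.786/0.50 = 1.57 | 0.700/0.30 = 2.33 | 0.914/0.80 = 1.14 |
| 5 | 0.857 | 0.929/0.50 = 1.86 | 0.900/0.30 = 3.00 | 0.971/0.80 = 1.21 |
| upper bound | 1 | 1/0.50 = 2.00 | 1/0.30 = 3.33 | 1/0.80 = 1.25 |

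**Step 2: what a true benefit would look like.** Multiply the ratios for 1 to 5 days by the true rate ratio.

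- True 30% reduction (× 0.7): 0.90 to 1.30 under 5 years, and 1.17 to 2.10 over 5 years.
- True halving (× 0.5): 0.64 to 0.93 under 5 years, and 0.83 to 1.50 over 5 years.

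A modest benefit in participants over 5 would show as an increase. A large benefit in children under 5 would keep its direction but look smaller than it is.

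**Step 3: all infections, with MSAT.** Let *s* be the share of infections with fever and *r* the chance that MSAT finds one without fever. Both are assumed: *s* from 0.2 to 0.8 and *r* from 0.3 to 0.9, with 2-day fevers.

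- Arm 3 to arm 1: [*s*·*p* + (1 − *s*)·*r*]/(*s*·*c*).
  - Lowest (*c* = 0.50, *s* = 0.8, *r* = 0.3): (0.571 + 0.06)/0.40 = 1.6.
  - Highest (*c* = 0.30, *s* = 0.2, *r* = 0.9): (0.12 + 0.72)/0.06 = 14.
- Arm 3 to arm 2, same two settings: 0.631/0.571 = 1.1, and 0.84/0.12 = 7.

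The range is wide because *s* and *r* are unknown. Every value lies above 1.

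**Step 4: would passive cases alone solve it?** No. An infection treated through CCM or MSAT may never reach the clinic, so a ratio of passive cases is biased the other way.

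**The case against.** **Detection is itself an aim.** Gradual implementation of interventions describes the study's purpose as establishing how well the interventions detect infections, and Box 3 counts infections as detected. As yield, a higher count in arms 2 and 3 is the intended result. This stands. The fault lies in giving the count the name of incidence and comparing it with an arm that lacks two of the three routes.

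**No fall in incidence is hypothesised.** The stated hypotheses concern prevalence and density, and the design deliberately keeps transmission unaffected. This also stands, and the reductions in Step 2 are illustrations. But if exposure is meant to be alike across arms, much of any excess in arms 2 and 3 would come from looking harder.

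**The coverage figures are modelling inputs.** The trial's clinics have research staff and supplies, treatment is free, and participants must be willing to use the designated facilities. Actual arm 1 capture is unknown and may be well above 50% and 30%. At 80% the bias is small, though still upwards.

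**The analysis plan may settle it.** A plan could add detail on how routes are combined. However, the article already fixes both the routes and the between-arm comparison, so this is a stated choice and not an omission.

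**A stronger reading is tempting.** A reader might infer that the ratio measures detection instead of incidence, or that an intervention which lowers incidence must appear to raise it. The documents do not support either. The ratio contains both components, which cannot be separated. Box 1 catches only fever at the visit or in the preceding 24 hours, so 2.0 and 3.3 are upper bounds, and a true halving need not show as a rise.

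**Conclusion.** The concern holds in a limited form. The secondary end point counts infections through routes that differ by arm, and the article compares that count between arms. As a measure of incidence the ratio is inflated for arms 2 and 3, and it can mask or reverse a benefit.

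For clinical cases, arm 2 against arm 1, the inflation at equal true incidence is:

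- at most 2.0 (under 5) and 3.3 (over 5) with the simulation's passive coverage;
- about 1.3 to 1.9 and 1.7 to 3.0 if fevers last 1 to 5 days;
- about 1.07 to 1.25 if passive coverage were 80%.

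The direction follows from the nested routes. The size rests on simulation inputs and on assumed fever duration, independent capture and RDT positivity.

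It would be wrong to infer that the trial's main comparison is compromised. The primary end point comes from one molecular survey applied to all arms and is not affected. Nor are the counts without value, since as detection yield they answer a question the study asks. This is a should-fix for one of eight secondary end points.

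**What to change.** 1. **Rename and separate the counts.** Report CCM, MSAT and passive detections by route as detection yield, and state that their between-arm ratio is not a measure of incidence.
2. **Keep one route-specific comparison.** Fever cases found by CCM may be compared between arms 2 and 3, which share the same weekly screening. Note that treatment through MSAT is part of that contrast.
3. **Take incident infection from common sampling.** Base any between-arm comparison on the 10-weekly routine and the cross-sectional qPCR surveys. Start person-time at risk only after a negative survey sample, or use genotyping to identify new clones where it is done.

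This changes end-point wording and analysis and needs no new visits. Wider use of genotyping would be an added cost, because Laboratory assessments plans it for selected samples only.

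The repaired comparison is still not fully arm-neutral:

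- Short infections treated between surveys will be missed more often in arms 2 and 3.
- Infections are not cleared at entry, and symptom-free PCR-positive infections are not treated, so persistent carriage in arm 1 can hide new infections.
- Requiring a negative sample takes persistent carriers out of both events and person-time, but the people left at risk may then differ between arms.

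The result should carry these caveats. It would still be closer to incidence than a count whose detection route is randomised.
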